## Abstract

**Background:**

Since 2007, the German statutory health insurance covers Specialized Outpatient Palliative Care (SAPV). SAPV offers team-based home care for patients with advanced and progressive disease, complex symptoms and life expectancy limited to days, weeks or months. The introduction of SAPV is ruled by a directive (SAPV directive). Within this regulation, SAPV delivery models can and do differ regarding team structures, financing models, cooperation with other care professionals and processes of care. The research project SAVOIR is funded by G-BA’s German Innovations Fund to evaluate the implementation of the SAPV directive.

**Methods:**

The processes, content and quality of SAPV will be evaluated from the perspectives of patients, SAPV teams, general practitioners and other care givers and payers. The influence of different contracts, team and network structures and regional and geographic settings on processes and results including patient-reported outcomes will be analyzed in five subprojects: [1] structural characteristics of SAPV and their impact on patient care, [2] quality of care from the perspective of patients, [3] quality of care from the perspective of SAPV teams, hospices, ambulatory nursing services, nursing homes and other care givers, content and extent of care from [4] the perspective of General Practitioners and [5] from the perspective of payers.

The evaluation will be based on different types of data: team and organizational structures, treatment data based on routine documentation with electronic medical record systems, prospective assessment of patient-reported outcomes in a sample of SAPV teams, qualitative interviews with other stakeholders like nursing and hospice services, a survey in general practitioners and a retrospective analysis of claims data of all SAPV patients, covered by the health insurance fund BARMER in 2016.

**Discussion:**

Data analysis will allow identification of variables, associated with quality of SAPV. Based on these findings, the SAVOIR study group will develop recommendations for the Federal Joint Committee for a revision of the SAPV directive.

**Trial registration:**

German Clinical Trials Register (DRKS): DRKS00013949 (retrospectively registered, 14.03.2018), DRKS00014726 (14.05.2018), DRKS00014730 (30.05.2018). Subproject 3 is an interview study with professional caregivers and therefore not registered in DRKS as a clinical study.

## Background

Corresponding to the Federal Statistical Office about 1% of the population in Germany dies within a year [1] and studies as well as the German Association for Palliative Medicine (DGP) estimate that about 90% of these require some level of palliative care [2–5]. To facilitate understanding of palliative care provision in the German health care system in the international community, we use the terminology defined by the European Association for Palliative Care (EAPC) in the “White Paper on standards and norms for hospice and palliative care in Europe” [6, 7]. According to the EAPC, palliative care can be made available on three different levels: palliative care approach, general palliative care and specialist palliative care – whilst palliative care approach and general palliative are often dealt as a joint category when focusing on the contrast to specialist palliative care, as we will do during this study protocol. While most patients with a life-limiting disease may only require general palliative care as provided by primary care professionals or specialists, a substantial amount of patients suffer from a high burden of symptoms and therefore require specialist palliative care. In case of outpatient care in Germany, general palliative care can be provided as General Outpatient Palliative Care (AAPV) and patients with a need for specialist palliative care can be referred to Specialized Outpatient Palliative Care (SAPV). SAPV is regularly provided by multi-professional home palliative care teams, comprising at least physicians and nurses, delivering specialized palliative care at the homes of patients with complex needs and suffering from incurable, progressive and life-limiting diseases.

Since the German Act to Strengthen Competition in Statutory Health Insurance (GKV-WSG) was introduced in 2007, SAPV has been fully covered by the Statutory Health Insurance [8] and can be prescribed by outpatient physicians as general practitioners (GPs),or by hospital physicians. Eligibility criteria as well as type and extent of SAPV services are determined by the SAPV directive of the Federal Joint Committee (G-BA, the highest decision-making body of the joint self-government of physicians, dentists, hospitals and health insurance funds in Germany) [9]. The SAPV directive defines objectives of SAPV (§1), eligibility requirements (§2, §3), particularly complex care (§4), content and scope of SAPV (§5), collaboration with other care providers (§6), prescription of SAPV (§7) and the assessment of entitlement for benefits by health insurance funds (§8). This directive has been worded in general terms to enable health insurance funds and care providers to make individual agreements (selective contracting), based on regional specifications and already existing structures. The resulting regulations are highly variable regarding care provision, cooperation and quality assurance as well as financial reimbursement and has led to different models [10]. This is reflected in over 290 different SAPV contracts nationwide [11], so that team structures, cooperation with other care givers, patient inclusion and exclusion criteria, processes of care, treatment intensity and financing models may differ substantially between the SAPV teams.

In 2016 about 55.000 patients (6% of the deceased in Germany) had received SAPV [11] before their death. This proportion is well below the estimated 10% of dying patients with a need for specialist palliative care at home [2]. However, recent analyses in Germany focused mainly on the description of (regional) SAPV-structures and utilization [12–16] as, for instance, the study “Faktencheck Gesundheit” investigated regional disparities of SAPV prescriptions [17]. Until now, no nationwide assessment of SAPV from different perspectives has been conducted [18]. In our view, there is a special need for an evaluation of the SAPV directive taking into account:The heterogeneity of organizational structures and processes and their effects on patient care: Heterogeneity is particularly represented by different forms of ownership, team structure, integration of different professions, reimbursement systems and regional factors like urban or rural settings [14]. This also leads to different levels of involvement of the SAPV teams (consultation, coordination of care, partial or full provision of care). The potential consequences of these different contractual elements on patients´ care are mostly unknown.As palliative care is a multi-professional, patient-centered care model, different perspectives of affected persons and involved professionals should be considered [19].Although the individual needs of patients and their relatives are key aspects of the SAPV directive, there are no formal requirements for a corresponding quality assurance. Available research does not focus on the patient perspective at all [17] or only does so in specific scenarios [14, 20]. Assessing quality of care without consideration of the patients perspective will remain incomplete [21]. With the help of the questionnaire QUAPS (Quality Assurance in Outpatient Palliative Care) we will be able to investigate quality of SAPV from patients’ perspective [22].Since SAPV is acting in a complex social environment of patients, relatives and health care professionals, the evaluation of overall quality of palliative care requires an adapted and differentiated analysis considering cooperation and perspective of these stakeholders. Accordingly, SAPV is a process of interactions of these participants, located in the individual patient’s environment. Therefore it is necessary to describe the local cooperation of health care professionals.General practitioners (GP) are substantially involved in the end of life care of their patients [23]. They play an important role in AAPV, can introduce SAPV to patients’ care by medical prescription and often remain subsequently involved [24]. This key role strengthens the need of assessing the impact of GPs on the quality of SAPV in connection to patients, other health professionals and the SAPV directive.The interface between general and specialist outpatient palliative care appears to be under-explored [11, 25]. Furthermore, available claims data studies focused on a small selection of specific aspects of palliative care [26]. Investigation of utilization and costs of different types of palliative care using claims data is a useful addition. On that basis it might be possible to find hints for over-, under- and missupply of end-of-life-care considering health economic perspectives.Against the background of the requirements of the national ethics council [27], it is an important goal to highlight the patients’ welfare as the leading principle in medical care. Taking this into account, it is necessary to focus on potential shortage of outpatient palliative care in specific patient groups, for example patients with non-malignant disorders.

So far, a systematic and nationwide data assessment in SAPV is lacking. In order to support the further development of SAPV and the guiding SAPV directive, it is necessary to assess the process, extent and quality of SAPV and their determining factors. For this purpose, SAVOIR (Evaluation of the SAPV directive, Outcomes, Interactions and regional variations) was funded by the German Innovations Fund (launched by the Federal Joint Committee) to evaluate the execution of the SAPV directive and to present suggestions for a revision of the SAPV directive.

The project is performed by the Department of Palliative Care (coordinator), Institute of General Practice and Family Medicine (both Jena University Hospital), Clinic for Palliative Medicine (University Medical Center Göttingen), Center for Interdisciplinary Health Research (ZIG, University of Augsburg), German federal association for SAPV (BAG-SAPV), German Association for Palliative Medicine (DGP) and the health insurance fund BARMER.

## Methods/design

### Aim of the study

The project will study care provision in SAPV from the perspective of patients, SAPV teams, other care givers, GPs and payers. The influence of different contracts, team and network structures, regional and geographic settings on processes and results including patient-reported outcomes will be analyzed. This will be carried out in five subprojects:

**Subproject 1:** The aim is to investigate the structural characteristics of SAPV (determined by contracts and organizational team structures) and assess if and how these aspects influence patient care.

**Subproject 2:** The aim is to investigate the quality of care from the perspective of patients.

**Subproject 3:** The aim is to estimate the quality of care from the perspective of SAPV teams and external network partners such as hospices, ambulatory nursing services, nursing homes and other care givers.

**Subproject 4:** The aim is to investigate the type and extent of GPs palliative care with and without SAPV and the quality of palliative care from their perspective.

**Subproject 5:** The aim is to describe and distinct different types of palliative care, the patients receiving these types of care, their health care utilization and quality of care in its regional variations by means of health insurance fund claims data.

Primarily, mixed-methods data analysis will allow the identification of variables that influence care provision and may be associated with quality of SAPV. Based on these findings, the SAVOIR study group will provide recommendations for the revision of the SAPV directive for the Federal Joint Committee.

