### Design and setting

The project will be based on different data sources: subproject 1a) registry data on team and organizational structures from the German Guide for hospice and palliative care services as well as model contracts in all German regions and 1b) clinical routine patient data from electronic medical record (EMR) of a sample of SAPV teams, subproject 2) patient-reported outcomes in a sample of about 50 SAPV teams, each collecting data from 25 patients, subproject 3) qualitative interviews with members of SAPV teams and linked providers involved in SAPV, like nursing and hospice services, subproject 4) survey data from GPs and subproject 5) health insurance fund claims data from patients who have died in 2016 and were covered by the health insurance fund BARMER.

This study is conducted in Germany from July 2017 to June 2019 and includes a transdisciplinary and multi-method design. The overall project is characterized by a cross-project use of data and a combination of quantitative and qualitative research designs. The focus of the quantitative research is obtaining a representative cross-section of the German SAPV, for instance by mapping the 17 Regional Associations of Statutory Health Insurance Physicians (KV). These regions are equivalent to the 16 Federal German States, but North Rhine-Westphalia is divided into North Rhine and Westphalia-Lippe.

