##### Study population

Step 1a/1b: Comprehensive assessment of SAPV teams and contracts. Step 2: Recruitment of 4 teams per region (*n* = 17). Assessment of 70 patients per team in six months, resulting in 5.950 patient data sets.

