**Subproject 1:** In step 1a, teams may not provide their real personnel structures, but rather a socially desirable version. The interviews were conducted via phone, which may increase this effect. The regulatory contracts may not cover the “real care provision”, as there may be regional differences that were not captured in the interviews and that we are unaware of. Some regions have model contracts, but specific characteristics like financial reimbursement may still vary between teams. To assess patient care, we use clinical routine data. While our prospective assessment enables us to give the teams information about the extracted data in advance and thus provide a better data quality, clinical routine data still is difficult to interpret. The variables used may be differently understood by those who document them and thus result in various interpretations within and between collecting SAPV teams.

**Subproject 2:** Questioning palliative patients and their relatives can only be pursued under several limitations: Patients are often in a poor general condition, participation in research is an additional burden for them and palliative care teams are often not experienced in clinical research and are reluctant to address participations. A specific challenge is given by the fact that life expectancy in SAPV patients is often limited to days or few weeks and treatment ends in most cases with the death of the patient. Therefore, in contrast to most other types of care, it is not possible to approach patients at the end of SAPV treatment. On the other hand, patients have to have experienced a certain time of SAPV care before they can report on its quality. Therefore, there is only a small time window to obtain patient-reported information on quality of SAPV care [35]. This may reduce the sample size and those participating may be a selected group of relatively “healthy” patients. However, pilot testing has revealed that the chosen approach will result in a sufficient number of data sets. Therefore we conduct a multi-method design, collecting treatment data of all patients agreeing to participate in subproject 1 over the time of recruitment for subproject 2.

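### Where a region's sampled teams share a contract term, its association with care cannot be told from that of other regional factors, yet the aim lists contracts and regional setting as influences to be analysed

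*Protocol article*

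**What the plan says.** - **Aim of the study:** "The influence of different contracts, team and network structures, regional and geographic settings on processes and results including patient-reported outcomes will be analyzed". The same section says that recommendations for revising the directive will be based on the findings.
- **Background:** contracts are agreed between insurers and providers "based on regional specifications and already existing structures". On how varied the result is: "This is reflected in over 290 different SAPV contracts nationwide".
- **Design and setting:** the data sources for subproject 1 include "model contracts in all German regions".
- **Subproject 1, Study population:** "Recruitment of 4 teams per region", with 17 regions. No section says that teams are chosen to differ in contract within a region. Design and setting refers in passing to selection criteria for teams shared across subprojects, but does not name contract among them.
- **Subproject 1, Data analyses:** hierarchical multilevel models relate structural predictors to patient and care parameters.
- **Discussion, Subproject 1:** "Some regions have model contracts, but specific characteristics like financial reimbursement may still vary between teams". This sits uneasily with the statement in Design and setting, and the two bear directly on how much contract terms vary within a region.

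**The concern.** A revision of the directive can act on contract rules but not on a region's supply, geography or history. Whether an observed difference belongs to the contract or to the region therefore decides what may be recommended.

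Regional conditions come before the contract and help to shape it, so region is a candidate confounder of any contract association. Sampling is stratified by region and not by contract. If the few teams sampled in a region work under the same term, nothing inside that region separates the term from everything else those teams have in common. A multilevel model allows for clustering and gives suitable standard errors, but it does not remove this confounding. A random-region model will still return a contract coefficient, and nothing in that coefficient shows how much of it comes from comparing regions.

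**Working it through.** **Inputs from the protocol.** Four teams per region and 17 regions give 4 × 17 = 68 teams (Subproject 1, Study population). Subproject 2, which supplies the patient-reported outcomes, has 50 teams, or 50 / 17 = 2.9 per region. There are over 290 contracts (Background), or 290 / 17 = 17.1 per region if spread evenly; the spread is not given. The number of regions whose sampled teams share a given term is not stated, so it is varied here from 0 to 17.

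The protocol gives no figure for the separability of contract and region, so there is none to reproduce. Its patient total for subproject 1 does not follow from its inputs: 4 × 17 × 70 = 4,760, not 5,950, which equals 5 × 17 × 70. That is a separate inconsistency. With five teams per region the argument below is unchanged in kind.

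**Step 1: estimability.** Take a team-level model with 17 region indicators and one binary contract term, 18 columns in all. If the term is uniform inside every region, its column is a sum of region indicators. The matrix has rank 17 of 18, and the term is not estimable with region in the model. If at least one region contains both values, the rank is 18 and the term is estimable.

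**Step 2: within-region degrees of freedom.** Each region whose teams differ contributes at most 4 − 1 = 3. With m uniform regions the maximum is 3 × (17 − m): 51 for m = 0, 36 for m = 5, 21 for m = 10 and 0 for m = 17.

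**Step 3: illustration of precision and bias.** The following are assumptions, not protocol figures: total outcome variance 1; region variance 0.05; team variance t = 0.05 or 0.10; 70 patients per team; non-uniform regions split two against two; uniform regions alternating between the two values; and a regional difference of 0.20 SD that follows the region mean of the contract term.

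- Variance of a team mean within a region: v = t + (1 − t − 0.05) / 70, which is 0.0629 or 0.1121.
- Within-region information: I_W = (17 − m) × 1 / v, since a two-against-two split gives 4 × 0.25 = 1 per region.
- Between-region information: I_B = S / (0.05 + v / 4), where S is the sum of squares of the region means of the term.
- Fixed-region SE = 1 / √I_W.
- Random-region SE = 1 / √(I_W + I_B).
- Random-region bias = 0.20 × I_B / (I_W + I_B).

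Worked case, m = 13 and t = 0.05. I_W = 4 / 0.0629 = 63.6. Six regions have mean 1, seven have mean 0 and four have mean 0.5, so S = 3.235 and I_B = 3.235 / 0.0657 = 49.2. The fixed-region SE is 0.125, the random-region SE is 0.094, and the bias is 0.20 × 49.2 / 112.9 = 0.087.

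| Uniform regions (of 17) | Fixed-region SE | Random-region SE | Random-region bias |
|---|---|---|---|
| 0 | 0.061–0.081 | 0.061–0.081 | 0 |
| 4 | 0.070–0.093 | 0.067–0.088 | 0.014–0.020 |
| 9 | 0.089–0.118 | 0.079–0.100 | 0.042–0.057 |
| 13 | 0.125–0.167 | 0.094–0.114 | 0.087–0.108 |
| 17 | not estimable | 0.125–0.136 | 0.20 (in full) |

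Ranges run from t = 0.05 to t = 0.10. As more regions are uniform, the random-region model keeps a moderate standard error by drawing on between-region contrasts, and it takes on regional confounding in the same proportion.

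**The case against.** **Contracts vary a great deal.** The Background says that the directive lets insurers and providers make individual agreements, and it counts over 290 contracts. The Discussion adds that reimbursement may differ between teams even where a model contract exists. This stands. A reader might infer from "as well as model contracts in all German regions" that each region has a single set of terms, so that contracts carry no within-region information at all. The documents do not support that: a model contract is not proof of identical terms, and the Discussion attributes model contracts to some regions only. The last row of the table is a limiting case, not a description of this study.

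**Regional setting is wider than KV region.** The Background gives urban or rural setting as an example of a regional factor, and this can vary among teams within one KV region. This also stands. The difficulty concerns what a region's sampled teams have in common, not geography as such.

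**Model details belong in an analysis plan.** How region enters the model may properly be left to a plan not shown, and the stated multilevel approach is compatible with the fix below. But no analysis plan can create within-region variation that the sampled teams lack.

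**The language is mostly associational.** Subproject 1's hypothesis and analysis speak of associations, and the aim does not expressly promise mutually adjusted effects. This largely stands. What remains is the word influence in the aim, tied to recommendations.

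**Limits are acknowledged.** The Discussion concedes that not all differences can be taken into account and that regional differences may go uncaptured. It does not say that contract and region may be inseparable.

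**Conclusion.** The point holds in conditional form. For any contract term that a region's sampled teams share, that region adds nothing to the within-region estimate, and what it contributes through between-region contrasts is confounded with other regional factors. This follows from the sampling design and needs no numerical assumption.

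How far it affects this study cannot be computed from the documents, because they do not say which terms vary among the sampled teams. The standard errors and biases in the table rest on assumed variances, an assumed regional difference and an assumed pattern of sharing. They show the direction and the dependence on the number of uniform regions. A reader might take them as a forecast of bias in the study's results, which the documents do not allow.

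The matter is worth acting on because the findings feed recommendations on the directive. It does not undermine the study's descriptive value.

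**What to change.** 1. With KV region as a level above team, split each contract predictor into its region mean and the team's deviation from that mean, and report both coefficients.
2. Adjust the between-region coefficient for area variables such as population density.
3. For each contract term, report how many regions show variation among the sampled teams. Do this separately for subproject 2, where there are fewer teams per region.
4. Label terms that are uniform within regions 'contract or region, not separable', and base no contract-specific recommendation on them alone.
5. In Aim of the study, replace influence with association.

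The within-region coefficient need not be the only basis for conclusions. Relying on it alone trades precision for less bias, and it still leaves differences between teams inside a region uncontrolled. Reporting both lets the reader see whether they agree.

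The cost is limited to analysis and wording, with no new data beyond area variables. The downside is wider intervals for within-region contract associations and no contract-specific conclusion for region-uniform terms.
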